### Experimental plan and data analysis

Based on the medical literature, the mean incidence of the combined frequency of mortality and severe neurodevelopmental disability in survivors at 18 months of age is approximately 50%. In fact this percentage is 55% in the cool Cap study
[66], 44% in the NICHD study
[68], 45% in the TOBY trial
[69], 51.4% in the ICE trial
[70], and 50.9% in the neo.nEURO.network study
[71]. We hypothesize that treatment with TPM may reduce the incidence of the combined frequency of mortality and severe neurodevelopmental disability in survivors at 18 months at 15%. In order to compare the incidence of this primary outcome between newborns receiving TPM plus hypothermia (treated) and those only receiving hypothermia (control group), the estimated sample size was calculated, considering normal distribution, an alpha error of 0.05 and a power of 80 percent. The sample size for each group is 32 participants.

The three units have an overall admission rate of approximately 10 term newborns with HIE per year. Due to the high hypothetical advantages of this treatment, we estimate 90-100% rate of consent and we predict we would recruit the 64 newborns over around 24 months period with a realistic safety margin.

Mortality, the incidence of severe neuromotor disability, cortical vision, sensorineural hearing loss, developmental delay, epilepsy will be evaluated at 18 months of life.

To evaluate TPM safety, cardiac and respiratory parameters (heart frequency, blood pressure, oxygen saturation, respiratory support), will be continuously monitored. Blood samplings will be performed to check renal, liver and metabolic balance. Kruskal-Wallis test will be used to assess possible differences between newborns treated or not with TPM. The safety will be also evaluated by means of relative risk (RR)
[132]. RR will be calculated as the ratio between the probabilities of side effects in the TPM group with respect to the control group. Values of RR lower than 1, will be associated to the efficacy of the treatment.

Finally, we will evaluate the different distribution of any brain lesions on MRI brain highlighted.The RR is calculated for each item studied. An RR <1 indicates an improvement of neurological, neurodevelopmental and neuroradiologic hypothermia due to the association-topiramate.

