#### Monitoring

The following respiratory and hemodynamic parameters will be registered before starting hypothermia and then at hours 0, 6, 12, 18, 24, 30, 36, 42, 48, 54, 60, 66, 72 of hypothermia, and after the re-warming process: respiratory rate, oxygen saturation (SaO_2_), fractional inspired oxygen (FiO_2_), systolic, diastolic and mean arterial pressures, heart rate. The following blood tests will be performed in all newborns at hypothermia hours 0, 24, 48, 72 and after re-warming process: blood gas analysis (corrected for body temperature), serum electrolytes, liver and renal function tests, creatine-kinase, creatine-kinase MB isoenzyme, lactate dehydrogenase, troponin IC, complete cell blood count, C-reactive protein, procalcitonin and coagulation tests.

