#### Clinical course and concomitant treatments

A central venous line will be placed in all patients. Fluid intake will be started at 60–70 mL/kg and increased of 10–20 mL/kg each day, basing on changes in body weight and serum electrolytes levels. Minimal enteral feeding will be allowed with human milk from the first day of life. In case of respiratory failure newborns will be put on patient triggered ventilation. Neonates who will develop seizures will be treated with phenobarbital, (loading dose 20 mg/kg, followed by 1.5-2.5 mg/kg every 12 hours). In case of resistance to phenobarbital, midazolam will be used with a dose-initial bolus of 0.15 mg/kg, followed by a continuous infusion (1 μg/kg/min) increased by 0.5-1 μg/kg/min every 2 minutes until a favourable response and up to a maximum dose of 18 μg/kg/min
[117]. In case of hypotension, defined as a mean arterial blood pressure <40 mmHg, single or multiple normal saline boluses will be administered (10–20 mL/kg), and in case of refractoriness, dopamine, dobutamine, norepinephrine or terlipressin
[119] will be progressively added. Newborns will receive analgesia with Fentanyl at a dose of 1 μg/kg/h, since hypothermia causes agitation and reducing the threshold of pain.

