#### Secondary endpoint

a. To evaluate the safety of TPM treatment, cardiac and respiratory parameters (heart frequency, blood pressure, oxygen saturation, respiratory support) will be continuously monitored; blood samplings will be performed to check renal, liver and metabolic balance

b. To evaluate if TPM improves the functional and structural outcome, visual function is planned at 40 weeks gestational age, 4 ½, 12, 18 and 24 months corrected age.

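### Recorded blood pressure is compared for safety after low values have been treated, and no safety or monitoring list includes the circulatory support given, so the comparison is biased towards no difference

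*Protocol article*

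**What the plan says.** *Objectives* names safety of topiramate as the first purpose. The haemodynamic and respiratory safety variables appear there, in *Experimental plan and data analysis* ("cardiac and respiratory parameters (heart frequency, blood pressure, oxygen saturation, respiratory support), will be continuously monitored") and in *Secondary endpoint* ("cardiac and respiratory parameters (heart frequency, blood pressure, oxygen saturation, respiratory support) will be continuously monitored"). *Monitoring* lists what is registered before cooling, at 13 fixed times (hours 0 to 72, every 6 hours) and after re-warming: "respiratory rate, oxygen saturation (SaO_2_), fractional inspired oxygen (FiO_2_), systolic, diastolic and mean arterial pressures, heart rate".

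Two analyses are planned. The first is "Kruskal-Wallis test will be used to assess possible differences between newborns treated or not with TPM". The second is a relative risk: "RR will be calculated as the ratio between the probabilities of side effects in the TPM group with respect to the control group". The side effects are not listed.

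*Clinical course and concomitant treatments* says: "In case of hypotension, defined as a mean arterial blood pressure <40 mmHg, single or multiple normal saline boluses will be administered". It continues, "in case of refractoriness, dopamine, dobutamine, norepinephrine or terlipressin" being added progressively. Neither step is restricted to one arm.

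Fluid boluses and vasoactive drugs appear in none of the three safety lists and not in the monitoring schedule.

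**The concern.** A variable that staff correct once it crosses a threshold is a poor measure of what pushed it across. If topiramate lowers pressure, more treated infants fall below 40 mmHg, receive support, and are then recorded at a restored pressure. Part of the drug effect moves from the variable that is compared into one that is not listed for comparison. Registration at 6-hour points adds to this, because an episode treated between two points may leave no low value in the record.

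The stated aim is to confirm safety, so a finding of no difference in blood pressure would be read as success. *Discussion* says the dose is raised from 5 to 10 mg/kg and that hypothermia and organ injury may alter drug handling, which makes an attenuated safety comparison more costly.

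**Working it through.** **The plan's own figure.** The document gives no figure for the safety comparison. Its only sample-size figure is 32 per group, for 50% v 15% on the primary outcome, alpha 0.05, power 80%. The two-sided pooled formula gives n = [1.96·√(2·0.325·0.675) + 0.8416·√(0.25 + 0.1275)]² / 0.35² = (1.298 + 0.517)² / 0.1225 ≈ 26.9. The continuity correction gives (26.9/4)·[1 + √(1 + 4/(26.9·0.35))]² ≈ 32.4. The figure reproduces (33 when rounded up). It matters here only as the number per arm.

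**Inputs from the protocol.** Treatment threshold 40 mmHg; 32 per arm; 13 registered readings during cooling; Kruskal-Wallis test.

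**Assumptions, none in the documents.** Untreated mean pressure 45 mmHg, SD 8, normal. A true fall *d* of 5 or 8 mmHg on topiramate. A value below 40 is replaced, with probability *s*, by a supported value with mean 45.

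**Step 1: how far the difference shrinks.** With untreated mean μ and a = (40 − μ)/8:

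- p = Φ(a) is the share below 40.
- U = μ(1 − p) + 8φ(a) is the part of the mean from values at or above 40.
- L = μ − U is the part from values below 40.
- Recorded mean = U + s·p·45 + (1 − s)·L.

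Control (μ = 45): p = 0.266, U = 35.66, L = 9.34. Topiramate with d = 8 (μ = 37): p = 0.646, U = 16.07, L = 20.93.

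- s = 1: control 35.66 + 11.97 = 47.63; topiramate 16.07 + 29.08 = 45.14. Difference 2.48 instead of 8, a loss of 69%.
- s = 0.5: control 46.31; topiramate 41.07. Difference 5.24, a loss of 34%.

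For d = 5 (μ = 40: p = 0.5, U = 23.19, L = 16.81) the difference is 1.93 at s = 1 (loss 61%) and 3.47 at s = 0.5 (loss 31%). The range is about 30% to 70%.

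**Step 2: detection with one reading per infant.** Simulation, 2,000 trials per setting, supported values N(44, 3), Fisher's exact test on receipt of support:

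| True fall | Pressure, untreated | Pressure, support works 50% / 80% / 100% | Receipt of support |
|---|---|---|---|
| 4 mmHg | about 49% | 35% / 30% / 27% | 24–27% |
| 6 mmHg | about 82% | 61% / 48% / 43% | 56–57% |
| 8 mmHg | about 97% | 81% / 66% / 55% | 83–84% |

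**Step 3: detection with the 13 registered readings.** Kruskal-Wallis on infant means, every reading below 40 eligible for correction, no carry-over between readings.

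- Within-infant correlation 0.5: pressure detects a 5 to 8 mmHg fall 69–100% of the time. Any reading below 40 does so 34–66% of the time by Fisher's exact test. With complete correction and an uncorrected chi-square test, it does so 51% of the time at 5 mmHg and 85% at 8 mmHg, against 69% and 94% for pressure. The binary measure is weak here because about 75% of controls meet it.
- Correlation near 0.9 with complete correction: the order reverses, with 51% for pressure v 90% for any reading below 40 at 8 mmHg.

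The difference shrinks in every setting. Whether that costs much power, and which measure is more sensitive, depends on the assumptions.

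**The case against.** **The relative risk of side effects could capture hypotension.** The protocol defines hypotension, and *Secondary outcomes* counts adverse events by organ system. Nothing excludes hypotension from either. This stands as a possibility, but neither passage says that hypotension or circulatory support is counted, and the organ-system outcome needs three or more systems, so isolated hypotension would not reach it.

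**An article leaves case-report fields to the full protocol.** That is fair, and the full documents may record these drugs. But the article does not stay silent: it states the safety variables three times and gives a registration schedule, with support listed on the respiratory side only. That stated choice is what is at issue.

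**Hypotension is not among the topiramate risks that *Objectives* discusses.** This is true, and the 5 to 8 mmHg falls are illustrative. Blood pressure is nevertheless a safety variable the protocol itself chose.

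**Stronger readings that the documents do not support:**

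- That drug-induced hypotension would be largely hidden, or that raw pressure should become descriptive only. Step 3 shows pressure often remains the more sensitive measure.
- That the error always favours the drug. The bias is towards no difference; if the drug raised pressure, the same mechanism would hide that too.
- That oxygen saturation has the same gap. Respiratory support is in the safety lists, inspired oxygen is registered, and no saturation target is stated.
- That bicarbonate treatment masks acidosis. The passage in *Objectives* describes earlier reported patients, and the trial's concomitant-treatment section gives no bicarbonate rule.

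**Conclusion.** The point holds for circulation. Recorded pressure is measured after threshold-driven treatment, the treatment is outside every listed safety comparison, and the arm difference is biased towards no difference in the study's first objective. Under the assumed pressures a true 5 to 8 mmHg fall loses about 30% to 70% of its size. The loss of power ranges from negligible to severe, depending on how often support succeeds and on the within-infant correlation, and the documents fix neither. A null pressure comparison alone therefore cannot confirm haemodynamic safety, but it is not uninformative, and the remedy is to add to it rather than replace it.

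**What to change.** In *Monitoring*, *Experimental plan and data analysis* and *Secondary endpoint*:

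1. Add volume boluses and vasoactive drugs given for hypotension to the recorded safety data.
2. Keep the Kruskal-Wallis comparison of pressure. Beside it, compare by arm, with the relative risk already planned for side effects, the proportion of infants with any mean pressure below 40 mmHg (the protocol's own definition) or any circulatory support for hypotension.
3. Report by arm the highest support step reached in the protocol's existing sequence.
4. State that no difference in blood pressure will not be read as confirming safety without items 2 and 3.

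Episodes below 40 mmHg should be taken from the continuous monitoring or the chart as well as the 6-hour points. The cost is a few chart-derived fields and a short addition to the analysis text. One drawback is that decisions to give support are not described as blinded and could differ by arm, so the below-40 component should also be reported separately. With 32 per arm the combined measure may itself have low power, which is a further reason to keep pressure. Clinical management does not change.

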### Objectives

#### Major objectives: safety and efficacy of TPM associated with moderate whole-body hypothermia

The first purpose of this study is to confirm the safety of TPM administration in asphyxiated newborns. For this purpose, cardiac and respiratory parameters (heart frequency, blood pressure, oxygen saturation, respiratory support), will be continuously monitored. Blood samplings will be performed to check renal, liver and metabolic balance.

TPM is considered to be safe and generally well tolerated in children. The safety profile of TPM might be different in neonates with HIE treated with hypothermia than in adults receiving chronic therapy for epilepsy. TPM can cause metabolic acidosis, especially in pediatric patients, because of carbonic anhydrase inhibition at proximal renal tubule with consequent renal loss of bicarbonate
[106,107]. In as many as 48% of adults and 67% of children with epilepsy treated with TPM, a variable degree of metabolic acidosis develops. However, in most reported cases, bicarbonate levels did not decrease to be clinically significant. Only 11% of patients had serum bicarbonate levels <17 mEq/L
[106,108] and symptomatic cases were successfully treated with sodium bicarbonate supplementation
[106]. Although this observation is reassuring, metabolic acidosis is usually severe in neonates with HIE, who have metabolic acidosis because of both asphyxia and renal impairment. In infants, metabolic acidosis usually occurs after 8 to 26 days of TPM treatment, with dosages as high as 8.2 to 26 mg/kg/day
[109]. Similar to other carbonic acid anhydrase inhibitors, long-course TPM therapy is associated with increased risk of nephrolithiasis in adults
[106,107]. Angle closure glaucoma and acute myopia are additional, though potentially reversible, adverse events related to TPM treatment in the pediatric age
[106,107,110]. In a safety study, we found no signs of metabolic acidosis in newborns co-treated with moderate hypothermia and TPM; abdomen ultrasound scanning did not show kidney stones and ophthalmological evaluation was normal in all treated newborns
[104].

The second objective of this study is to evaluate the efficacy of TPM add-on therapy, evaluating the clinical outcome of enrolled newborns. The neurological and neuroradiologic outcome of newborns treated with hypothermia plus TPM will be compared to the outcome of control group that received hypothermia alone.

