## Discussion

The objective of this research is highly ambitious: to find a treatment procedure that is simple, inexpensive, well tolerated and with few adverse effects, able to reduce post-ischemic neuronal damage. Neuroprotection is a major health care priority, given the enormous burden of human suffering and financial cost caused by perinatal brain damage. Hypothermic treatment is recognized as a neuroprotective treatment after a profound neonatal insult. However, it is clear from previously published clinical trials and animal studies that hypothermia alone does not provide complete protection. Neuroprotective drugs added during or after hypothermia might improve neurologic protection, by extending the therapeutic window or providing long-lasting additive or synergistic action
[133]. This combination treatment could open new perspectives for the management of asphyxiated infants. To date, no clinical study has evaluated the efficacy of the combined treatment hypothermia and TPM, an antiglutaminergic drug mainly used for the treatment of epilepsy. On the other hand, it is important to consider that drugs administered during the neonatal period may be dangerous to the immature brain, and hypothermia can modify their pharmacokinetics. In fact, excretion of many drugs and their metabolites can be modified by hypothermia; failure of liver and kidney clearance due to hypoxic-ischemic injury could exacerbate any toxicity. In newborns with HIE, TPM pharmacokinetic properties appear to be modified by concomitant hypothermia, but the dosage of 5 mg/kg appears safe. In this study the dosage will be increased to 10 mg/kg, likewise in other studies. For this reason one of the main objectives of this study is to confirm the safety of TPM added to hypothermia.

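### Safety is to be confirmed, but a test of difference and a side-effect relative risk read against 1, at 32 per arm sized for efficacy, cannot support a no-harm conclusion

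*Protocol article*

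**What the plan says.** The objective is stated twice in the protocol article. Under *Major objectives*: "The first purpose of this study is to confirm the safety of TPM administration in asphyxiated newborns". In the *Discussion*, after noting that the dosage is higher than the one studied before: "For this reason one of the main objectives of this study is to confirm the safety of TPM added to hypothermia". Under *Secondary endpoint* the wording is milder, and safety ranks below efficacy: "To evaluate the safety of TPM treatment, cardiac and respiratory parameters" are to be monitored and blood tests taken.

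The analysis is in *Experimental plan and data analysis*. For the cardiac, respiratory and laboratory parameters, "Kruskal-Wallis test will be used to assess possible differences between newborns treated or not with TPM". The next sentences add a second safety analysis, the ratio of side-effect probabilities in the TPM and control groups, with this reading: "Values of RR lower than 1, will be associated to the efficacy of the treatment". Neither analysis comes with an interval, a margin or a largest harm to be ruled out.

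The sample size in the same section is derived from the primary efficacy outcome, 50% against 15%, "considering normal distribution, an alpha error of 0.05 and a power of 80 percent". The result is: "The sample size for each group is 32 participants". No safety quantity enters that calculation.

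**The concern.** Confirming safety is a conclusion that harm is absent or small. A Kruskal-Wallis test has no difference as its null hypothesis. It can reveal harm, but it can speak for safety only by failing to reject, and at this size failing to reject is weak evidence. The relative risk does not fill the gap. A point value compared with 1 says nothing about how large a harm is still compatible with the data.

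The stakes come from the article itself. It describes metabolic acidosis under TPM and says acidosis is usually severe in these infants. It reports reduced TPM clearance under hypothermia, and it gives the increased dosage as the reason why safety is a main objective. A reassurance that the data cannot bear would pass into later studies in newborns.

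**Working it through.** **Inputs from the article:** 32 per arm, 1:1 allocation, alpha 0.05, power 80%, event rates 50% and 15%. **Assumptions:** two-sided alpha (sidedness is not stated), one value per infant, independent infants, and the shift sizes and side-effect counts below. The article gives no SD, safety effect size or side-effect rate.

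**1. The plan's own figure.** With a pooled rate of (0.50 + 0.15)/2 = 0.325:

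n = [1.96·√(2·0.325·0.675) + 0.8416·√(0.50·0.50 + 0.15·0.85)]² / 0.35² = (1.298 + 0.517)² / 0.1225 ≈ 26.9, so 27 per arm.

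With continuity correction: n = (26.9/4)·[1 + √(1 + 4/(26.9·0.35))]² ≈ 32.4, or 33 rounded up. The stated 32 is reproduced to within one infant, from efficacy inputs only.

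**2. Power of the named test.** Simulated two-group Kruskal-Wallis test, 32 per arm, 20,000 runs, normal data:

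| True shift (SD) | Power |
|---|---|
| 0 | 4.8% |
| 0.3 | 21% |
| 0.5 | 48% |
| 0.7 | 77% |
| 0.8 | 87% |

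- Power of 80% is reached at about 0.72–0.74 SD.
- Analytic check at 0.5 SD, using the rank-test efficiency 3/π: Φ(0.5·√(32·(3/π)/2) − 1.96) = Φ(1.954 − 1.96) ≈ 50%.
- For an assumed lognormal distribution (log-SD 0.5) shifted by 0.5 SD, power is about 68%.

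**3. What 32 per arm can exclude.** The 95% CI half-width for a difference in means is t(0.975, 62)·√(2/32) = 2.00·0.25 = 0.50 SD. If TPM truly had no effect, the interval would exclude a 0.5-SD harm with probability Φ(0.5/0.25 − 1.96) = Φ(0.04) ≈ 52%. Doing so with 80% probability would take 2·(1.96 + 0.8416)²/0.5² ≈ 63 per arm at one-sided 0.025, or 50 at one-sided 0.05.

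**4. The relative risk.** Suppose 4/32 against 4/32: SE(log RR) = √(2·(1/4 − 1/32)) = 0.661, so RR = 1.0 with 95% CI exp(±1.96·0.661) = 0.27 to 3.66. With 6/32 against 6/32 the interval is 0.36 to 2.77. When the true risks are equal, at 10% to 30%, exact enumeration puts the observed RR below 1 in 42–45% of trials. Power to detect a rise from 10% to 20% is about 20%, and from 20% to 40% about 41%.

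**The case against.** The strongest reply is that the article contains no rule equating non-significance with safety. It says only that differences will be assessed, which is an ordinary way to look for harm. A reader might infer that the plan treats p > 0.05 as proof of safety. The text does not say so, and that reading should not be attributed to it.

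A reader might also infer that the Kruskal-Wallis test is the only safety analysis. It is the only named hypothesis test, but the relative risk is a second analysis. Safety is further supported by scheduled readings and blood tests, daily clinical evaluation and an interim analysis.

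The trial is a phase II pilot, and the *Secondary endpoint* section speaks of evaluating safety. Sizing on efficacy and describing safety is normal for such a trial. Intervals may also appear in a full protocol or SAP that is not shown, so their absence from an article is not by itself a fault.

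Finally, 0.5 SD is not the protocol's figure. Power is clearly higher under skew, which is plausible for enzymes and creatinine, and the repeated readings per infant are not modelled here.

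All of this narrows the point and softens it. It does not remove the mismatch in what the article does state: an objective worded as confirmation, and analyses that can only describe or detect. The written rule for reading the relative risk rests on its value against 1, not on an interval.

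**Conclusion.** The concern holds in a limited form. At 32 per arm, the stated safety analyses cannot deliver the stated no-harm conclusion. That follows from the logic of a difference test without a bound and does not depend on any chosen effect size.

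The size of the problem does depend on assumptions. For normal data, Kruskal-Wallis power runs from about 21% at 0.3 SD to 86–87% at 0.8 SD, with 48–49% at 0.5 SD. A blanket statement that a half-SD harm would be missed more often than not is not supported, because under the lognormal assumption the miss rate at 0.5 SD is about 32%. For side effects, equal counts of four per arm would still be compatible with a more than threefold increase.

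This calls for correcting the objective and the way safety is inferred. It does not make the trial unsuitable as a pilot.

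**What to change.** - **Experimental plan and data analysis.** For the key safety parameters (at least bicarbonate or base excess, creatinine, liver enzymes, heart rate and mean arterial pressure), report the TPM-minus-control difference, as a mean or Hodges-Lehmann estimate, with a 95% CI. For side effects, report the risk difference and relative risk with 95% CIs.
- **Same section.** State that any safety statement will rest on the harm-side confidence limit, that is, on the largest harm the data exclude. It will not rest on a non-significant p-value or on a relative risk below 1.
- **Major objectives and Discussion.** Replace the aim of confirming safety with estimating the safety profile, labelled exploratory. Note that 32 per arm gives a 95% CI half-width of about 0.5 SD.

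The cost is a few sentences and routine intervals, with no extra infants, data or procedures. The downside is a more modest safety claim.

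### The two-group Kruskal-Wallis test named for safety does not fit serially recorded parameters, and a non-significant result from it cannot confirm safety

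*Protocol article*

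**What the plan says.** The objectives put safety first: "The first purpose of this study is to confirm the safety of TPM administration in asphyxiated newborns". The later section on measurement of outcomes lists safety as a secondary endpoint.

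The Monitoring section fixes the data as repeated series. The vital-sign parameters are "respiratory rate, oxygen saturation (SaO_2_), fractional inspired oxygen (FiO_2_), systolic, diastolic and mean arterial pressures, heart rate", recorded before cooling and "then at hours 0, 6, 12, 18, 24, 30, 36, 42, 48, 54, 60, 66, 72 of hypothermia, and after the re-warming process". The blood tests begin with "blood gas analysis (corrected for body temperature), serum electrolytes, liver and renal function tests, creatine-kinase, creatine-kinase MB isoenzyme, lactate dehydrogenase, troponin IC" and add blood count, C-reactive protein, procalcitonin and coagulation. They are taken at hours 0, 24, 48 and 72 and after re-warming.

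The data analysis section gives two safety analyses. The first is for the monitored parameters: "Kruskal-Wallis test will be used to assess possible differences between newborns treated or not with TPM". The second is for events: "RR will be calculated as the ratio between the probabilities of side effects in the TPM group with respect to the control group". An alpha of 0.05 appears in that section only for the sample size of the efficacy outcome. No level, time point, per-infant summary or acceptable limit is stated for safety.

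**The concern.** With two arms, Kruskal-Wallis is the two-sided Wilcoxon rank-sum test. It compares one independent value per infant and has no repeated-measures form. The protocol collects up to 15 values per infant for each vital sign and 5 for each blood item, and the analysis sentence does not link the two.

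Taken as written, the sentence can be applied in three ways:

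- a separate test at each time point, which multiplies the tests;
- a test on all serial values together, which treats one infant's readings as if they came from different infants;
- a test on one summary per infant, which is valid but not specified.

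The choice among them decides whether a reported TPM-control difference means anything. A further problem holds under all three: a difference test that fails to reach significance is not evidence of no harm, yet the stated aim is to confirm safety.

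**Working it through.** **Inputs from the protocol**
- Vital-sign parameters: respiratory rate, SaO2, FiO2, three arterial pressures, heart rate = 7. Occasions after hour 0: 12 (hours 6 to 72) + 1 after re-warming = 13.
- Blood items: 12, counting liver and renal tests separately. Several are panels, so 12 is a floor. Occasions after hour 0: 24, 48, 72 h and after re-warming = 4.
- 32 infants per arm. This is the plan's only related figure. For 50% against 15%, two-sided 0.05 and 80% power, the continuity-corrected formula gives 33 (27 uncorrected), so 32 is reproduced to within one. It concerns efficacy; the plan gives no figure for safety.

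**Assumptions, not in the documents:** 0.05 per test, normally distributed series, correlation 0.5 between parameters, within-infant correlation 0.5 to 0.8 (exchangeable or first-order autoregressive). All false-positive rates are under no drug effect.

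**1. A test at each time point**

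Number of tests: 7 × 13 + 12 × 4 = 91 + 48 = 139. Simulated chance of at least one p < 0.05 (3,000 replicates, 32 per arm, rank test):

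| Family | Exch. 0.5 | Exch. 0.8 | AR 0.5 | AR 0.8 |
|---|---|---|---|---|
| One vital sign, 13 occasions | 0.35 | 0.20 | 0.44 | 0.32 |
| 7 vital signs | 0.90 | 0.68 | 0.95 | 0.87 |
| One blood item, 4 occasions | 0.16 | 0.13 | 0.16 | 0.13 |
| 12 blood items | 0.73 | 0.63 | 0.77 | 0.67 |

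An independent repeat gave about 71-95% for the vital signs and 62-75% for the blood items.

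**2. Serial values pooled into one test**

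With m values per infant and within-infant correlation ρ, the variance of the arm difference is understated by a factor of about 1 + (m − 1)ρ. The approximate false-positive rate is therefore 2[1 − Φ(1.96/√(1 + (m − 1)ρ))].

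| m | ρ | Factor | Formula | Simulated |
|---|---|---|---|---|
| 13 | 0.2 | 3.4 | 0.29 | 0.28 |
| 13 | 0.5 | 7.0 | 0.46 | 0.43 |
| 13 | 0.8 | 10.6 | 0.55 | 0.55 |
| 4 | 0.2 | 1.6 | 0.12 | 0.12 |
| 4 | 0.5 | 2.5 | 0.22 | 0.20 |
| 4 | 0.8 | 3.4 | 0.29 | 0.29 |

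**3. One mean per infant**

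Simulated false-positive rate: 0.046-0.054 per parameter. Across 7 + 12 = 19 parameters the chance of at least one false difference is 1 − 0.95^19 = 62% if they are independent. Simulation with between-parameter correlation from 0 to 0.7 gave about 36-64%. This is why the individual comparisons still need to be read as estimates.

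**4. Missed harm**

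- The difference that a single two-sided test detects with 80% power is (1.96 + 0.84) × √(2/32) = 2.80 × 0.25 = 0.70 SD (normal approximation).
- A true 0.5 SD shift gives z = 0.5/0.25 = 2.0, so power is about 52% by the normal approximation and 48-50% in simulation of the rank test. It would be missed about half the time.
- If the shift is sustained over three occasions, the variance of the mean is (1 + 2ρ)/3 of that of one value. At ρ = 0.5 this is 0.667, z = 2.0/√0.667 = 2.45, power 69%. At ρ = 0.8 it is 0.867, z = 2.15, power 57%. Simulations gave 54-66% and, in a repeat, 56-70%.

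**The case against.** The strongest reply is that the protocol does not prescribe testing at each time point or pooling. Its monitoring schedule is not a testing schedule, and a rank test on one summary per infant would be valid. The summary measure and the handling of multiple safety comparisons are often left to an analysis plan, which is not shown here. The 0.05 level is borrowed from the efficacy calculation. The trial is a pilot, and unadjusted safety tables are ordinary in a pilot, where sensitivity to harm matters more than familywise error. Most of this stands. The absence of a multiplicity rule is no fault in itself, and the 139 tests are one reading, not a stated plan.

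A reader might infer four stronger claims, which the documents do not support:

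- *A spurious difference is near certain.* That needs every time point tested at 0.05, which is not stated. With one test per parameter the figure is about 36-64%.
- *Safety rests on Kruskal-Wallis alone.* The relative risk of side effects is also planned, although it has no stated limit and the text links values below 1 to efficacy.
- *False positives would lead to a wrong declaration of safety.* They work the other way. A wrong declaration comes from missed harm, and a Bonferroni correction over 19 parameters would raise the detectable difference from 0.70 to about 0.96 SD.
- *Bicarbonate must be the single decisive test.* The objectives discuss acidosis at length but also name kidney stones, glaucoma and myopia. They mention bicarbonate supplementation in reported cases, which could mask such a contrast. One test without an acceptable limit could not confirm safety either.

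What the reply does not remove is that the one method stated for these data makes no use of their repeated structure, and that the aim is worded as confirmation.

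**Conclusion.** The concern holds in limited form. The named test does not match serial data, and two of its three possible applications perform poorly. Testing at each time point makes at least one false difference likely, at about 68-95% over the vital signs and 62-77% over the blood items. Pooling gives a false-positive rate of about 12-55% for a single test. A per-infant summary holds about 5% per parameter and, for a sustained 0.5 SD shift over three occasions, raises power from about 48-50% to 54-70%. These figures rest on the assumed 0.05 level, normality and correlations; the count of parameters and occasions and the 32 per arm come from the protocol. Separately, neither the rank tests nor the relative risk has a limit against which safety could be judged, so a non-significant result from either cannot confirm it. The change should be made, but it concerns interpretability and does not invalidate the trial.

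**What to change.** In the data analysis section, replace the Kruskal-Wallis sentence with these rules:

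1. Make one TPM-control comparison per parameter. Use either a per-infant summary of the values after hour 0 (for example their mean), or a mixed model with infant as random effect, the hour-0 value as covariate and one overall treatment contrast.
2. Report each comparison as a difference with its 95% CI, and show blood-gas bicarbonate/base excess prominently because the objectives discuss acidosis.
3. Label comparisons at individual time points as descriptive.
4. State that a non-significant difference, or a relative risk whose interval includes 1, is not read as confirmed safety.

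No familywise correction is requested, since it would make harm harder to detect. The cost is analysis wording only, because all the data are already scheduled for collection. The one loss is that a brief effect at a single time point is shown descriptively and not formally tested.
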